## Abstract

**Background:**

Germline genetic testing is recommended by the National Comprehensive Cancer Network (NCCN) for individuals including, but not limited to, those with a personal history of ovarian cancer, young-onset (< 50 years) breast cancer, and a family history of ovarian cancer or male breast cancer. Genetic testing is underused overall, and rates are consistently lower among Black and Hispanic populations. Behavioral economics-informed implementation strategies, or nudges, directed towards patients and clinicians may increase the use of this evidence-based clinical practice.

**Methods:**

Patients meeting eligibility for germline genetic testing for breast and ovarian cancer will be identified using electronic phenotyping algorithms. A pragmatic cohort study will test three sequential strategies to promote genetic testing, two directed at patients and one directed at clinicians, deployed in the electronic health record (EHR) for patients in OB-GYN clinics across a diverse academic medical center. We will use rapid cycle approaches informed by relevant clinician and patient experiences, health equity, and behavioral economics to optimize and de-risk our strategies and methods before trial initiation. Step 1 will send patients messages through the health system patient portal. For non-responders, step 2 will reach out to patients via text message. For non-responders, Step 3 will contact patients’ clinicians using a novel “pend and send” tool in the EHR. The primary implementation outcome is engagement with germline genetic testing for breast and ovarian cancer predisposition, defined as a scheduled genetic counseling appointment. Patient data collected through the EHR (e.g., race/ethnicity, geocoded address) will be examined as moderators of the impact of the strategies.

**Discussion:**

This study will be one of the first to sequentially examine the effects of patient- and clinician-directed strategies informed by behavioral economics on engagement with breast and ovarian cancer genetic testing. The pragmatic and sequential design will facilitate a large and diverse patient sample, allow for the assessment of incremental gains from different implementation strategies, and permit the assessment of moderators of strategy effectiveness. The findings may help determine the impact of low-cost, highly transportable implementation strategies that can be integrated into healthcare systems to improve the use of genomic medicine.

**Trial registration:**

ClinicalTrials.gov. NCT05721326. Registered February 10, 2023. https://www.clinicaltrials.gov/study/NCT05721326

**Supplementary Information:**

The online version contains supplementary material available at 10.1186/s13012-023-01308-w.

Contributions to the literature
•This study will evaluate novel sequential steps to promote the use of genetic testing to determine breast and ovarian cancer predisposition.•This study will be one of the first to use implementation strategies informed by behavioral economics directed to both patients and clinicians to increase the use of genetic testing for breast and ovarian cancer predisposition across a large health system.•This study may provide support for low-cost, simple, and scalable approaches to increasing the engagement of at-risk patients with breast and ovarian cancer genetic testing.

## Background

Breast cancer is the most common cancer for women across the world [1–3]. Approximately 300,000 new breast cancer cases were estimated in the USA for 2022, accounting for roughly one-third of new cancer diagnoses among U.S. women [4, 5]. Although less common, ovarian cancer ranks as the deadliest gynecologic cancer, accounting for about 20,000 cases and 13,000 deaths per year [4, 6, 7]. Moreover, substantial health inequities exist for both cancers. Early-stage diagnosis is critical for increasing survival rates [8, 9], but Black women tend to be diagnosed at later stages than white women [7, 10], and mortality rates for both diseases are > 30% higher for Black women as compared to white women [7, 11, 12].

In the past decade, multigene panel tests have been increasingly used to analyze several genes associated with breast and ovarian cancer [13–15]. Genetic testing can inform risk assessment, suggest interventions for risk reduction, and change options for therapy [16]. Multiple FDA approvals for PARP inhibitors for the treatment for BRCA-associated cancer, including early-stage, high-risk breast cancer [17, 18], have changed the landscape with regard to medical intervention [19]. As such, patients [20, 21] and clinicians [20, 22, 23] are generally interested in genetic testing and the National Comprehensive Cancer Network (NCCN) recommends testing for specific groups (e.g., people with personal histories of ovarian cancer) [14]. Unfortunately, there is a clear practice gap in genetic testing uptake, with only about 35% of ovarian cancer patients undergoing testing [24–27]. In assessing two large gynecology practices in our health system, we found higher rates than average of genetic testing among patients diagnosed within the last two years with early-onset breast cancer or triple-negative breast cancer. However, we found very low rates of genetic testing in individuals who were (1) diagnosed with ovarian cancer previously, or (2) had a family history of ovarian cancer or male breast cancer. Testing rates of those with a family history (rather than a personal history) of cancer were less than 15%. Moreover, substantial health inequities exist in testing rates. Eligible Black women are much less likely to be tested than their non-Hispanic white counterparts [11, 25–28], a finding replicated in the analysis of our own data, even with similar referral rates for all patients meeting our eligibility criteria.

Barriers to genomic medicine uptake exist at the system, clinician, and patient levels. The number of available genetic tests is growing exponentially [29, 30], so it can be challenging to integrate genomic data into the electronic health record (EHR) to track genetic test results and facilitate clinical workflows [31–33]. Our health system has tackled this issue by using Health Level 7 (HL7) standardization with labs, genomic indicators, and a precision medicine tab within the EHR [34]. However, due to expanding and changing indications and unclear eligibility criteria [35], clinicians may face challenges in identifying those eligible for genetic testing. Also, they report barriers related to a lack of awareness or training, cost concerns, and busy schedules [33, 35–39], resulting in uncertainty and lower priority for referring patients to genetic counseling. Integrating genomic medicine into the EHR can mitigate some concerns by identifying appropriate patients and guiding clinicians via streamlined workflows [34, 35, 40, 41]. Still, when faced with uncertainty, people often rely on cognitive heuristics to make decisions [42], such as status quo bias, or preferring to maintain the current state over taking action to change [40]. When perceiving unclear eligibility criteria or facing a busy schedule, clinicians may opt to keep things the same to maintain simplicity. The status quo bias can be leveraged by shifting the status quo to default genetics consult orders and emphasizing the availability of EHR-based support systems and clear recommendations for genetic testing. Similarly, default orders can make the referral process easier.

Given the shared decision-making dynamics underlying the choice to pursue genetic testing, patient barriers also must be addressed, including awareness [43–45], access [46], cost concerns [21, 43–47], anxiety about the potential misuse of test results [45, 48, 49], and insurance discrimination [21, 50]. Patients’ decisions are also affected by cognitive heuristics. Omission bias, or focusing on the potential harm of action more than that of inaction [51], plays a key role. Concerns about the implications of test results for patients and their families (such as the need for family members to be tested or fear about how medical professionals or insurance companies may use test results) can trigger omission bias and lead patients to think that getting genetic testing is worse than not pursuing it [52, 53]. These concerns tend to be heightened among members of racial or ethnic minority groups who have been mistreated by the medical system [45, 48, 49]. Although clinician recommendations to pursue genetic testing are one of the strongest predictors of patient willingness to undergo testing [28, 54, 55], clinicians are significantly less likely to recommend it to Black and Hispanic women [28, 54, 56]. Increasing the use of genetic testing requires addressing barriers at multiple levels [57], many of which are salient for patients from minoritized groups. Thus, offering patients the opportunity to be involved in decision-making about genetic testing is crucial for facilitating sustainable and equitable uptake [43].

Leveraging behavioral economic theory to mitigate cognitive heuristics has been effective in promoting evidence-based care and improving patient outcomes [58–62]. Nudges are strategies that make it easier for clinicians and patients to make evidence-based decisions. These can include framing language and/or default options, which subtly change the environment to facilitate evidence-based decisions while still preserving people’s freedom of choice [60, 63]. For instance, emphasizing the ease of genetic testing and the harms of not taking the first steps toward an appointment could mitigate omission bias. For clinicians, nudges can incorporate accountable justification, which requires clinicians to substantiate their decisions when declining a new status quo (in the form of a default order) and can promote self-reflection and higher-value care [64, 65].

Health system nudges have the potential to encourage uptake of genetic testing. These strategies can be automated, are scalable, and could mitigate health inequities [40, 62, 66, 67]. Prior research suggests that clinicians recommend genetic testing less often for non-white patients [28, 54, 56], but sequential dissemination of strategies could expand reach. Initial messages sent via the health system patient portal (MyPennMedicine; MPM) could generate initial interest via a “low-touch” message with minimal costs. Outreach via text messaging, which is more widespread [68], will be able to mitigate inequities resulting from differential patient portal access [69] and facilitate comparisons of outreach strategies. To reduce clinician burden, clinicians will only be contacted in the final phase. Literature suggests that clinician-directed default nudges, which sit atop the nudge intervention ladder, may be the most influential in changing behavior [62, 66].

This study was designed to evaluate the effects of three sequentially delivered patient- and clinician-directed implementation strategies informed by behavioral economics on the scheduling of genetic counseling appointments for patients with breast and ovarian cancer risk. We chose a sequential study design to determine the relative effects of the three strategies. Adaptive designs are gaining in use, including in oncology [70], since they can efficiently help identify the relative benefits of adding components of an intervention in relationship to the overall resources needed to sustain them. Behavioral economics and implementation science can be integrated to maximize the impact and equity of strategies seeking to encourage patients to pursue genetic testing [63].

## Methods

### Study design

This pragmatic study will use a non-randomized, sequential adaptive design to examine the effect of patient- and clinician-directed nudges informed by behavioral economics and delivered via the EHR for promoting the use of genetic testing for the identification of breast and ovarian cancer predisposition. Sequences are detailed in Fig. 1. Before the sequences begin, we will use electronic phenotyping procedures to identify a cohort of patients receiving care through two large OB-GYN clinics who are eligible for genetic testing for breast and ovarian cancer predisposition (based on information in the EHR), but who have no documentation of testing in the EHR [71]. Next, in the first sequence, all patients will be contacted via the MyPennMedicine (MPM) patient portal. Messages will be delivered twice, one week apart. The message will include direct information on patients’ cancer risk based on their genetic history, their ability to take action to address their risk, and how to contact the study team to schedule an appointment. Patients can reply directly to the MPM message, call the Cancer Risk Evaluation Program (CREP), or use an outreach-specific email address. Patients who do not engage with the CREP within three weeks will receive the next adaptive sequence, a direct text message targeting omission bias to promote breast and ovarian cancer genetic testing. Again, patients will receive two text messages, a week apart, and will be given three weeks to schedule an appointment. The text message program will be conducted through Penn Way to Health, an evidence-based patient engagement platform [72, 73]. Finally, if patients do not engage with the genetics team, their clinicians will receive an EHR-based nudge targeting status quo bias using the “pend and send” functionality with a pended genetics consult order as a default. A final 6-month observation period will track the scheduling of genetic counseling and genetic testing results for breast and ovarian cancer predisposition following clinician strategy delivery. Patient characteristics (e.g., age, race/ethnicity, nature of genetic risk) will be ascertained from the EHR and explored as moderators of the effectiveness of each sequence to promote genetic testing. This sequential adaptive design will allow for comparisons of which strategies work best across clinics and subgroups of patients.

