Clinician nudge	Best practice alert (BPA) with pended order for genetics counseling Key questions: • What is the best timing and mechanism for sending clinician nudges, since eligible patients won’t be in the clinic very often? • What are the key cognitive heuristics affecting genetic testing ordering?	Method: Meetings with experts in behavioral science, implementation science, health equity, and informatics; discussions with clinicians Key feedback: • Alert fatigue can cause annoyance for care team members • Clinicians preferred a pre-selected recommendation which can be signed efficiently • Status quo bias was a key barrier	“Pend and send” default order for genetic testing with accountable justification for clinicians who decline the order
Patient nudge	Sequential nudges delivered via the patient portal and text message Key questions: • What strategies can be used to overcome inequities in patient portal access? • What are the key cognitive heuristics affecting genetic testing uptake?	Method: Meetings with experts in behavioral science, implementation science and health equity; patient review; pilot tests which contacted 200 patients via the patient portal and text message with two potential nudges Key feedback: • Messages with a clear call to action up front can spur behavior change • Wording changes to increase readability would be valuable • Pilot tests revealed that the message emphasizing ease led to high engagement	Patient portal messages emphasizing ease and text messages emphasizing the importance of taking action to prevent cancer

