### Patient nudges (patient portal and text message)

The patient-directed strategies will be delivered via two mechanisms: the patient portal and text message. Figure 2 shows both patient-directed nudges. The content of the nudges was influenced by past research documenting that patients tend to focus on the potential adverse effects of action vs. inaction [52, 53, 80] and was reviewed and modified by a group of clinicians and patient partners. Eligible patients will initially be contacted via the patient portal. This “low-touch” implementation strategy can provide information about the impact of using patient health system portals to encourage the uptake of genetic testing. If patients do not respond, or if they are identified as not having a patient portal account, they will be moved to the second implementation sequence. In this sequence, patients will be sent text messages using similar content from the first sequence, encouraging them to sign up for genetic counseling appointments. Patients who do not respond to the first two nudges will be identified for the clinician's nudge.

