### Clinician nudge

Our preliminary formative work involved the development of prototype messages to integrate as nudges delivered to clinicians through the EHR. As with the patient nudge, we created multiple versions of the nudges and ascertained feedback from partners about the message content and design, as well as the method and timing of delivery. Also, the study team engaged with research from another study promoting genetic testing and adapted the wording and format of a clinician nudge to design a message considered most likely to receive clinician support.

Both study sites use Epic (Epic Systems Corporation, Verona, WI) to deliver care. Recent upgrades to Penn’s Epic instance introduced the “pend and send” capability. Using this process, the research team will create a pended order for a genetics consult for eligible patients who did not respond to prior patient-directed strategies. As detailed in Fig. 3, the clinician nudge will include text leveraging status quo bias, a default order for a genetics consult, and a requirement for clinicians to provide accountable justification if they decline the order. Clinicians can efficiently sign orders in the InBasket without needing to open each encounter separately. The consults are then routed directly to the CREP scheduling team, who will contact the patient to schedule an appointment with a genetic counselor. We pilot-tested the “pend and send” mechanism in the RCAs. Clinicians have been engaged at both clinics so that they are aware of this initiative and clinician education has been provided.

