## Discussion

This study will sequentially test the effects of patient-directed strategies, sent via the patient portal and text message, and EHR-based clinician-directed strategies, sent as “pend and send” default orders, on genetic counseling engagement in gynecology practices at two distinct Penn Medicine clinics. It builds upon Penn ISC3’s prior work [74, 75] implementing nudges to patients and clinicians by extending it to new populations who face additional barriers to engaging in evidence-based clinical practices. Sequential delivery mechanisms can reinforce the additive value of combining outreach via different communication channels, as well as facilitate comparisons between different patient outreach mechanisms. Additionally, the study demonstrates the value of RCAs and pilot testing strategies before implementing them at scale. By addressing barriers and heuristics that affect both patients and clinicians, this multi-level approach may help to define optimal strategies resulting in increased potential for success.

Substantial racial inequities exist in genetic testing, the timeliness of cancer diagnosis, and mortality rates. Implementing these strategies at diverse clinics in this study seeks to mitigate such inequities. While innovative treatments for BRCA-associated cancers (such as PARP inhibitors) are being approved, these innovations can exacerbate racial inequities in downstream outcomes and guideline-concordant receipt of these innovative treatments if genetic testing is not equitably implemented. In combination with existing racial inequities in clinicians’ recommendations for genetic testing, expanding inclusion criteria for genetic testing for all breast cancer patients may widen the divide in genetic testing uptake. Automated outreach via several communication channels aims to alleviate this inequity, and if successful, it can guide future outreach programs to extend health systems’ reach.

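### The fixed-order, non-responder design can show what each step adds, but it cannot rank the three strategies as the protocol says it will

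*Protocol article*

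**What the plan says.** Three places in the Protocol article claim that the design compares strategies with one another:

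- Background: "We chose a sequential study design to determine the relative effects of the three strategies".
- Methods, Study design: "This sequential adaptive design will allow for comparisons of which strategies work best across clinics and subgroups of patients".
- Discussion: sequential delivery can "facilitate comparisons between different patient outreach mechanisms".

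The planned analysis follows the same line. The Study design section compares the number of appointments after each sequence, and the sample size section states power for comparisons between stages.

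On the design itself, the Study design section says: "This pragmatic study will use a non-randomized, sequential adaptive design". The portal message comes first, text goes to those who have not engaged within three weeks, and the clinician nudge goes to those who responded to neither. The section on patient nudges adds one exception: patients without a portal account move to the text step. No concurrent comparison group, varied order or staggered start is described.

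The abstract's Discussion paragraph gives a narrower aim, that the design will "allow for the assessment of incremental gains from different implementation strategies".

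**The concern.** The second and third steps are not applied to the population that received the first. They go to patients who were already contacted and did not schedule, at a later time, while earlier messages may still be working. A lower yield at text than at portal could mean that text is weaker, or only that the readiest patients had already left. A higher yield could mean that text is stronger, or that it collected delayed portal responders. The data cannot tell these apart.

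The outcome window adds to the problem. The Measures section counts appointments within six months after each step, but the patient steps are three weeks apart, so the windows overlap.

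At stake is the use made of the results. A health system that reads the step rates as a ranking could drop the text or clinician step because of an artefact of the order.

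**Working it through.** The article gives no figure for the size of this problem. Its power statement (80% for a 5% improvement between stages) concerns precision, not confounding, and is not used here.

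**Inputs from the article:** about 3000 patients; fixed order portal, text, clinician; three weeks for each patient step; outcomes within six months after each step; appointment counts compared across steps.

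**Inputs not in the article, assumed here:** a mean response of 10% to any nudge, the spread of responsiveness between patients, and the delay to response. In checks 1 and 2 all three nudges are equally effective by construction, and every patient follows the full path.

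**1. Counts, all patients alike.** Each step reaches only those left.

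- Step 1: 3000 × 0.10 = 300
- Step 2: (3000 − 300) × 0.10 = 270
- Step 3: (2700 − 270) × 0.10 = 243

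The counts fall although nothing differs between the nudges.

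**2. Rates, patients differ.** Let each patient have a fixed probability of scheduling at any nudge, drawn from a Beta(a, b) distribution with mean a/(a+b) = 0.10 and k = a + b. Its SD is √(0.10 × 0.90/(k+1)). The rate at step j among those still unscheduled is a/(k + j − 1).

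| Heterogeneity | k | a | SD | Step 1 | Step 2 | Step 3 | Counts |
|---|---|---|---|---|---|---|---|
| Weak | 20 | 2 | 0.07 | 2/20 = 10.0% | 2/21 = 9.5% | 2/22 = 9.1% | 300/257/222 |
| Moderate | 5 | 0.5 | 0.12 | 0.5/5 = 10.0% | 0.5/6 = 8.3% | 0.5/7 = 7.1% | 300/225/177 |
| Strong | 1 | 0.1 | 0.21 | 0.1/1 = 10.0% | 0.1/2 = 5.0% | 0.1/3 = 3.3% | 300/135/86 |

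With a mean of 5% or 15% the pattern is the same: 5.0/4.8/4.5% to 5.0/2.5/1.7%, and 15.0/14.3/13.6% to 15.0/7.5/5.0%.

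**3. Can the order reverse?** In a simulation with a random intercept of SD 2 on the logit scale, text was made truly better than portal by an odds factor of 1.5. In the full population that is 12.9% against 10.0%. Observed in sequence, text gives 9.6% against 10.0%, so portal looks better. With an odds factor of 2.0 the order is right, but the true gap (15.2% against 10.0%) shrinks to 11.6% against 10.0%.

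**4. Carry-over works the other way.** Suppose only the portal message has any effect, with an exponential delay of median m weeks. The share of its responders after week 3 is 2^(−3/m). For m = 1 this is 2^(−3) = 12.5%; for m = 3 it is 2^(−1) = 50%, of which 25 points fall in weeks 3 to 6 and 25 points later. These patients would be credited to text and clinician steps that did nothing.

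Depletion lowers the later steps and carry-over raises them, so the net direction of the distortion is unknown.

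**5. Patients without a portal account.** For them text is the first contact. Setting them against portal-first patients compares people without an account with people who have one, and the Background itself describes portal access as unequal.

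**The case against.** The strongest reply is that the article already frames the study modestly. The abstract speaks of incremental gains, the Background goes on to describe the benefit of adding components, and the Discussion concedes that the trial is not randomized and points to later cluster randomized trials. The fixed order has a stated rationale: the low-cost contact first, clinicians last to spare them burden. The Study design sentence can also be read as comparing one step across clinics or subgroups.

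Much of this stands. Incremental yield is a sound aim, the order is defensible, and one step can be compared descriptively across clinics. But none of it withdraws the claims in the Background and Discussion, which are plainly between strategies. The one sentence on non-randomization does not mention depletion or carry-over.

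A reader might infer more than the documents support:

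- *That every patient follows one order.* Patients without a portal account do not.
- *That the article contradicts itself on message content.* Table 1 lists "Patient portal messages emphasizing ease and text messages emphasizing the importance of taking action to prevent cancer", while the section on patient nudges says "patients will be sent text messages using similar content from the first sequence". Similar content with a different emphasis is possible, and the messages are in Fig. 2, which is not available here.
- *That the scheduling contact in Step 3 is a hidden flaw.* The Clinician nudge section states openly that signed consults go to the scheduling team, "who will contact the patient to schedule an appointment with a genetic counselor". It is part of that strategy.
- *That the study must be randomized to be useful.* Its incremental aim does not require that.

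**Conclusion.** The point holds as a mismatch between claim and design. Differences between steps cannot be read as relative effects of the strategies, overall or within a clinic or subgroup. This follows from the fixed non-randomized order and the restriction of later steps to non-responders, and needs no numerical assumption.

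The size does depend on assumptions. With equally effective nudges and a 10% mean response, the apparent fall from Step 1 to Step 3 runs from about one tenth (10.0% to 9.1%) to two thirds (10.0% to 3.3%). The drop in counts, 300 to 243, needs no heterogeneity. The response rate, spread and delay are not in the article, so these figures show a range and do not predict the bias.

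The design can describe the cumulative yield of the whole sequence and the added yield of each step given the earlier ones. Reading that yield as caused by the step still assumes that background scheduling and carry-over are small.

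**What to change.** Restate the objective, the between-stage comparisons and the conclusions as the cumulative yield and the incremental yield of adding each step, in this order, among patients still unscheduled. Give each step's yield over the number still at risk, so that counts are not compared alone. Remove or qualify the claims in the Background, Study design and Discussion that the study ranks strategies, determines their relative effects or compares channels. Report patients without a portal account separately.

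When interpreting results, note that portal and text differ in emphasis as well as channel, and that Step 3 includes outbound scheduling contact.

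The cost is a change of wording, one extra reporting split and a more modest claim. Randomizing the order of the two patient steps would allow a portal-versus-text comparison, but it is an optional redesign of an approved, registered study and not part of this fix.
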